#### Content

The SALUD program consists of 1 individual intake session (at the start), 12 weekly group sessions, and 1 booster session. Each weekly session has its own theme and goals (summary in Table 1). The sessions’ themes are based on the GRRs and SRRs that were identified during the participatory intervention development: self-identity, social support, food literacy, disease acceptance, and stress management. A “learning by experience” approach will be used to equip participants with practical tools and skills. The coach uses several reflective (on- and off-screen) exercises related to diet, health, stress, and life during each session. The sessions are intended to be highly interactive and informal. Most sessions end with a practical home exercise (eg, “cook a new recipe this week”). A registered dietician will be invited to 1 of the sessions to answer specific nutrition-related questions. In 2 of the sessions, participants are encouraged to bring an important person (their best friend, partner, neighbor, or family member). Session 10 is deliberately left “open” to provide the participants with the opportunity to choose a topic based on their needs. More details about the intervention content can be found in the study by Polhuis et al [35].

#### Fidelity of Delivery

Fidelity of the intervention delivery is assured by the following:

selecting a coach in line with salutogenic principles, that is, whole person view on health and a participatory and empowering way of coachingusing a program manual in which the program’s core (salutogenic) values, the sessions, the exercises, and goals are outlinedthoroughly discussing with the coach about the (salutogenic) approach of the program before the start of the studyweekly evaluating forms that will be filled in by the coach after each session to keep track of deviations from the manual and feedback of participantsweekly checkups between the coach and the principal investigator (KP) to evaluate the previous session and to discuss the upcoming sessionrecording a (small) number of sessions (with permission of the participants).

### Control: Usual T2DM Care

The participants in the control group receive the usual Dutch T2DM care according to the Dutch General Practitioners Association (Nederlands Huisartsen Genootschap) protocols [37]. The usual care of T2DM is based on medical treatment, education, and lifestyle advice. Newly diagnosed persons and persons who require insulin administration are referred to a dietician by the GP. In some cases, the GP recommends a referral to a psychologist for help with dietary advice or to a physical therapist to help with physical activity. The GP refers to a specialist in case of complications (such as retinopathy and nephropathy). Generally, a person with T2DM has 4 quarterly checkups with the practice nurse and 1 yearly checkup with the GP. However, the exact frequency of the appointments depends on the specific agreements between the health care provider and the patient.

### Quantitative Evaluation

The primary outcome is food literacy; secondary outcomes are self-efficacy, QoL, SoC, diet quality (Dutch Healthy Diet Index 2015 [DHD-15 index]), body weight, BMI, and waist-hip ratio (WHR). Self-efficacy and SoC are measured to evaluate the empowerment process of the SALUD program; diet quality to assess changes in nutritional intake; QoL to assess effects on psychosocial health; and body weight, BMI, and WHR to assess the effects on physical health (Figure 2). All measurements take place at the participants’ homes.

**Figure 2 figure2:**
[figure not shown]
Proposed mechanism of action of the Salutogenic Intervention for Type 2 Diabetes (SALUD) program.

#### Food Literacy (Self-perceived Food Literacy Scale)

The self-perceived food literacy scale (SPFLS) [36] is used to determine the capability to make healthy food choices in different contexts, settings, and situations. The SPFLS is a relatively new tool developed by Dutch researchers and validated among healthy Dutch adults (with a high internal reliability; Cronbach α=.80) [36] as well in people who underwent kidney transplant [36,40]. In the general population and in the patients who underwent kidney transplant, higher food literacy was associated with a healthier nutritional intake [36,40]. The SPFLS scale is proven to be capable of distinguishing between different populations [36,40]. The SPFLS contains 29 items related to 8 domains: food preparation skills, resilience and resistance, examining food labels, daily food planning, healthy budgeting, and healthy food stockpiling, healthy snack manners, and social and conscious eating. Response options include a 5-point Likert scale (1=“not at all/never” to 5=“yes/always”), eventually providing a score between 29 and 145. A higher score indicates higher food literacy. Domain scores and a total score are computed for each participant. Permission to use the SPFLS in this research has been formally granted by the developers of the SPFLS.

#### Self-efficacy (Dutch General Self-Efficacy Scale)

The Dutch General Self-Efficacy Scale (DGSES) [41] is a unidimensional free accessible questionnaire that measures the confidence someone has in their own abilities to cope with external challenges. The original DGSES was developed in German and is currently adapted to 32 languages [41]. Internal consistencies yielded typically Cronbach α between .76 and .90 [41]. Criterion validity is documented in numerous correlation [41]. The DGSES consists of 10 questions related to how people generally think and act. The response options include a 4-point Likert scale (1=completely false; 4=completely true), eventually providing a score between 10 and 40, with a higher score indicating higher self-efficacy. A total score will be computed for each participant.

#### QoL (World Health Organization Quality of Life Questionnaire)

The Dutch and abbreviated version of the World Health Organization Quality of Life-100 (WHOQOL-100) questionnaire is used to determine how people perceived their QoL over the last 2 weeks [42]. The abbreviated WHOQOL-100 is known as WHOQOL-BREF. The WHOQOL-BREF has been validated by comparing it with the original WHOQOL-100 domain scores (domains scores correlate at around 0.9 with the original) [43]. Internal validity is high (Cronbach α>.70) [44]. The WHOQOL-BREF contains a total of 26 questions that assess 5 domains of health and well-being: general perceived QoL, physical health, psychological health, social relationships, and environment. Response option includes a 5-point Likert scale (1=not at all; 5=extremely true), eventually providing a score between 26 and 130. Higher scores denote better QoL. A score is computed for each QoL domain as well as a total QoL score. Permission to use the Dutch version has been granted by the World Health Organization.

#### Diet Quality (DHD-15 Index)

The DHD-15 index is used to assess the diet quality via a scoring system based on the Dutch food-based dietary guidelines [46]. The DHD-15 index is a relatively short food frequency questionnaire consisting of 40 questions. The DHD-15 index has been validated with 24-hour recalls and food frequency questionnaire data among Dutch adults with a Dutch dietary pattern [46]. The DHD-15 index calculates a score for 16 food components: vegetables, fruit, wholegrain products, legumes, nuts, dairy, fish, tea, fats and oils, coffee, red meat, processed meat, sweetened beverages and fruit juices, alcohol, salt, and unhealthy food products (snacks and cookies). Each component is scored on a scale ranging from 0 (implies nonadherence) to 10 (optimal adherence), eventually providing a total score between 0 and 160. A higher score indicates a more optimal diet quality (ie, a diet in line with the Dutch dietary guidelines). For the calculation of the scores, specific cutoff and threshold values were used as suggested by Looman et al [46]. A separate score for each component as well as a total score will be calculated. Formal permission to use the DHD-15 index was granted by the developers to the authors.

#### Anthropometry

Body weight is measured at the participant’s home with use of a scale (type: UC-411PBT-C) that measures to 2 decimals precisely. The scale will be calibrated before each measurement. The researcher makes sure the measurements are performed in similar circumstances (time of the day, placement of the scale, and layers of clothing). In addition to weight, height is measured once (during the first measurement). The scale calculates BMI (BMI [kg/m^2^]*=body weight [kg]/height [m]^2^*) and estimates fat percentage (%), muscle mass (kg), and basal metabolic rate (kcal).

#### Waist Circumference and WHR

Waist circumference and WHR are simple and useful measures of fat distribution. The measurements are performed according to the instructions of the World Health Organization [47]. In short, the participant must stand with arms at the sides, feet positioned close together, and weight evenly distributed across both feet. The measurement is performed at the end of a normal expiration. The researcher uses a measuring tape to measure the midpoint between the lower margin of the least palpable rib and the top of the iliac crest to determine waist circumference. Hip circumference is measured around the widest portion of the buttocks, with the tape parallel to the floor. All measurements are performed at the same time of the day (morning, afternoon, or evening). WHR is calculated using the following formula: *WHR=waist circumference (cm)/hip circumference (cm)*. A healthy WHR is considered ≤0.90 for men and ≤0.85 for women [47].

#### Participant Characteristics

A questionnaire consisting of personal contact details (name, age, address, phone number, and email), living situation, ethnicity, educational level, and clinical details (disease duration, medication use, and smoking [past and present]) is filled out during screening.

### Qualitative Evaluation

Consecutive to the 12th session, participants are invited to a focus group to provide feedback and share their personal experiences with the program. The participants’ partners are also invited to the focus group. One week before the focus group, the coach instructs the participants to bring an object that symbolizes their experiences with the SALUD and to think about what they liked or disliked about the program. The focus groups will be video recorded and used for qualitative effect analysis of the program. In the video recording, all participants (and partners) are asked to provide informed consent to record the session and to use the video recording for qualitative analysis. The following sample question will be used:

If you were the program director of SALUD, what would you change? Why?Would you recommend SALUD to other people? Why? Why not?What did SALUD mean to you? Which parts were valuable/useful for you?Which elements of SALUD were not valuable/useful for you?Did you change things in your everyday life because of SALUD (eg, daily life, interactions with others, and the way you think)? Why?

The video recording will be transcribed ad verbatim and pseudonymized. Two researchers of the research team analyze the transcripts independently. First, the transcripts are read and reread to engage with the data. Then, the transcripts are open coded on a descriptive and interpretative level. More specifically, transcripts will be coded on active components of the intervention, the mechanism of action, health-promoting resources, and the influence on everyday life. Subsequently, the codes are clustered in preliminary themes. Then, the 2 researchers compare and discuss the preliminary themes until consensus is reached. The overarching themes are the result of various discussions between the researchers. The themes will be displayed with pertinent participant quotes and detailed interpretative commentary. The Dutch quotes will be translated into English by a professional translator.

### Sample Size Calculation

Sample size calculation is based on the known mean value and SD of the SPFLS (food literacy measure) for the Dutch general population [36]. There are no RCTs with lifestyle interventions in the scientific literature that assessed food literacy (measured with SPFLS or another measure for food literacy) as a primary outcome. However, as RCTs evaluating lifestyle interventions that targeted psychosocial outcomes such as self-efficacy have demonstrated effect size of between 1.1 and 1.7 [48,49], it seemed reasonable to expect an effect size of 0.9. With use of the Cohen *d* calculation for effect size, an anticipated mean of 4.20 SPFLS score in the intervention group, and an anticipated mean of 3.83 (SD 0.41) in the control group is expected at T1 (based on references values [36]). With a standard power of 80% and a significance level of 5%, a total of 19 participants per group (38 participants in total) are needed. Adding a 30% dropout rate, the ideal sample size was set at 28 participants per group (56 in total).

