### Statistical Analyses

Statistical analyses are carried out using IBM SPSS Statistics for Windows, version 28 (released in 2021; IBM Corp). Two-sided *P* values <.05 are regarded as statistically significant. Analyses are performed with the intention-to-treat principle, meaning that all patients were analyzed in their original allocation group regardless of the extent to which they followed the intervention. Dropouts are counted, and reasons for dropping out are recorded. If missing is completely at random, all available data at T0 (baseline), T1 (12 weeks), and T2 (24 weeks) are used to conduct the analyses. If missing is at random, multiple imputation techniques are used to impute the missing data.

Scores are calculated for multiple-item instruments (ie, DGSES, WHOQOL-BREF, SoC-13, DHD-15 index, and SPFLS). Randomization will be checked, and variables will be normalized if needed. Descriptive statistics are performed to tabulate mean (or median) values of all study characteristics and baseline values of the independent variables. Chi-square tests (for categorical variables) and 2-tailed *t* tests (for continuous variables) are used to compare the descriptive statistics between study groups and to identify potential covariates. Data are tabulated as mean (SD) or median (IQR) if skewed. Categorical data are presented as n (%) where appropriate.

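### The stated 19 evaluable participants per group fall slightly short of 80% power on the plan's own inputs: 20 are needed by the normal approximation and 21 by the t-test

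*Protocol article*

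**What the plan says.** All the inputs are in the protocol article.

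- **Effect size** (Sample Size Calculation): by analogy with trials on self-efficacy, "it seemed reasonable to expect an effect size of 0.9".
- **Means and SD** (same section): the intervention arm is planned at 4.20. For the other arm, the text gives "an anticipated mean of 3.83 (SD 0.41) in the control group is expected at T1".
- **Error rates** (same section): the target is 80% power at the 5% level. The paragraph does not give the sidedness, but Statistical Analyses does: "Two-sided *P* values <.05 are regarded as statistically significant".
- **Result** (Sample Size Calculation): "a total of 19 participants per group (38 participants in total) are needed". This is then raised to 28 per group, 56 in total, for 30% dropout.

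The sample size section names no test or formula. Statistical Analyses plans mixed models using the measurements at baseline, 12 weeks and 24 weeks. The section on the food literacy scale describes 29 items scored 1 to 5, "eventually providing a score between 29 and 145".

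**The concern.** A required sample size is the smallest whole number that reaches the stated power, so a fractional answer is rounded up. The stated 19 appears to be a normal-approximation value rounded down. At about 19 per arm, the normal formula is also slightly optimistic, because it treats the SD as known.

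The stake is modest. The 19 is offered as what 80% power requires, the enrolment target of 28 is built on it, and readers will use it to judge what a non-significant primary result means.

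A smaller matter is the scale. Means of 3.83 and 4.20 cannot occur on a total that runs from 29 to 145. They look like averages over items scored 1 to 5, but the sample size section does not say so.

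**Working it through.** **Inputs.** Means 4.20 and 3.83; SD 0.41, given with the control mean and taken here for both groups; two-sided 5%; 80% power; 1:1 allocation. The difference is 4.20 − 3.83 = 0.37, so d = 0.37/0.41 = 0.902. Working back from the stated effect size, 3.83 + 0.9 × 0.41 = 4.199, which rounds to 4.20. So d = 0.90 may be the actual input and 4.20 its consequence. Both values are carried through.

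**Reproducing the plan's figure (normal approximation).** n per group = 2(1.960 + 0.842)²/d².

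- d = 0.902: n = 19.28
- d = 0.90: n = 19.38

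Rounded to the nearest integer this is 19, the plan's figure. Rounded up it is 20. A one-sided test gives 16, so sidedness does not explain 19.

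Power at n per group is Φ(d√(n/2) − 1.960). At n = 19 and d = 0.902 this is Φ(2.781 − 1.960) = Φ(0.821) = 79.4%. At d = 0.90 it is 79.2%.

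**Two-sample t-test (noncentral t, two-sided).** The required n is 20.28 (d = 0.902) or 20.39 (d = 0.90), so 21 per group, 42 in total.

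| Evaluable per group | t-test power, d = 0.90 / 0.902 | Normal-approximation power, d = 0.90 / 0.902 |
|---|---|---|
| 19 | 77.0% / 77.2% | 79.2% / 79.4% |
| 19.6 | 78.4% / 78.6% | 80.4% / 80.7% |
| 20 | 79.2% / 79.4% | 81.2% / 81.4% |
| 21 | 81.2% / 81.4% | not needed |

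By the t-test, the effect detectable with 80% power at 19 per group is d = 0.93, or 0.93 × 0.41 = 0.38 points, against the planned 0.37.

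**Dropout step.** 19/0.7 = 27.1, so 28 per group, which reproduces the plan. From 20 it would be 28.6, so 29. From 21 it would be exactly 30. The 28 enrolled leave 28 × 0.7 = 19.6 evaluable per group on average.

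**Scale.** If the total is 29 times the item average (an assumption, as the protocol gives no conversion), the planned difference is 29 × 0.37 = 10.7 points and the SD is 29 × 0.41 = 11.9 points. The ratio d is the same on both scales.

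**The case against.** The strongest reply is that the plan's figure is reproducible. No test is named, the normal approximation gives 19.3 to 19.4, and power at 19 is within one point of 80%. Carrying the unrounded value through the dropout step gives 19.28/0.7 = 27.5, which still rounds up to 28. At the 19.6 expected to remain, the normal approximation exceeds 80%. This stands, and it means the enrolment target cannot be called wrong on that formula. It does not rescue the statement that 19 are what 80% power needs, because 19 falls short under both formulas.

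A second reply is that the primary analysis is a mixed model with baseline data, not a two-sample t-test. This also stands. For illustration only: if baseline adjustment multiplies the variance by 1 − r², bringing 20.3 down to 19 takes r of about 0.25. The protocol gives no correlation, so the gain cannot be computed.

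A third reply is rounding of the printed inputs. Taken to their extremes, the two means and the SD allow d from 0.867 to 0.938. At the top of that range the t-test needs 18.8, so 19 would suffice; at the bottom it needs 21.9, so 22. The most favourable extreme cannot be excluded, but neither the printed values nor the stated 0.9 yields it.

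Readers might infer three stronger things:

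- **That the trial has 77% power and that 21 per group is the only right answer.** This holds only for a t-test on 19 per group, which the protocol neither names for the sample size nor plans for the primary outcome.
- **That more participants should have been enrolled.** The shortfall is too small and too dependent on the formula to support that.
- **That the scale mismatch undermines the calculation.** It does not, because d and power are unchanged by a factor of 29.

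**Conclusion.** The stated 19 evaluable per group is slightly too low for 80% power on the protocol's own inputs. The required number is 20 by the normal approximation and 21 by the t-test, the more suitable check at this size. Power at 19 is about 79% and 77% respectively. With 28 enrolled and 30% lost, about 19 to 20 per group remain, giving about 79 to 81% by the normal approximation and 77 to 79% by the t-test.

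These figures assume a common SD of 0.41, independent observations and a comparison at 12 weeks without baseline adjustment. Power under the planned mixed model may be higher by an amount the protocol does not allow one to compute. The shift in detectable effect, from 0.90 to 0.93, is small beside the uncertainty in an effect size borrowed from other outcomes. The scale mismatch is presentational.

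**What to change.** Restate the paragraph without enrolling more; the Results section reports that data acquisition is complete.

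1. Name the formula used and state that the calculation is two-sided.
2. Replace the claim about 19. For example: 28 enrolled per group with 30% dropout leave about 19 to 20 evaluable, giving about 77 to 79% power for d = 0.90 by two-sided t-test (about 79 to 81% by normal approximation), before any gain from baseline adjustment in the mixed model. Reaching 80% takes 21 evaluable per group by t-test, or 20 by normal approximation.
3. Say that the planning means and SD are item averages on a 1 to 5 scale, if that is so, or convert them to the 29 to 145 total. Under the factor of 29, that is a difference of about 10.7 points and an SD of about 11.9.

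The cost is a few sentences and a slightly less favourable power figure. No conduct or analysis changes.

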### Statistical Analyses

Statistical analyses are carried out using IBM SPSS Statistics for Windows, version 28 (released in 2021; IBM Corp). Two-sided *P* values <.05 are regarded as statistically significant. Analyses are performed with the intention-to-treat principle, meaning that all patients were analyzed in their original allocation group regardless of the extent to which they followed the intervention. Dropouts are counted, and reasons for dropping out are recorded. If missing is completely at random, all available data at T0 (baseline), T1 (12 weeks), and T2 (24 weeks) are used to conduct the analyses. If missing is at random, multiple imputation techniques are used to impute the missing data.

Scores are calculated for multiple-item instruments (ie, DGSES, WHOQOL-BREF, SoC-13, DHD-15 index, and SPFLS). Randomization will be checked, and variables will be normalized if needed. Descriptive statistics are performed to tabulate mean (or median) values of all study characteristics and baseline values of the independent variables. Chi-square tests (for categorical variables) and 2-tailed *t* tests (for continuous variables) are used to compare the descriptive statistics between study groups and to identify potential covariates. Data are tabulated as mean (SD) or median (IQR) if skewed. Categorical data are presented as n (%) where appropriate.

According to a strict data analysis protocol, primary and secondary outcomes are tested with mixed models. Secondary outcomes are also tested if the primary outcome is not statistically significant. The analyses scripts will be written by the researchers; the analysis of the primary outcome will be run by an independent researcher who is blind to the intervention code. Assumptions for mixed models are checked. The mixed models will test the difference compared with baseline in the scores and values (ie, dependent variables) between intervention and control (ie, independent variable) at T1 and T2. Fixed effects are the treatment condition, time, and the covariates; random effects are the repeated measures per participant at T0, T1, and T2. Multiple models are tested; a crude model, and additional models that are adjusted for confounders commonly adjusted for in literature (eg, sex, age, education, and BMI). Variables that statistically significantly differed at baseline are also included in a model as covariates. The final results are presented in a table displaying the estimated marginal means, 95% CIs, and *P* values for the treatment effect for all primary and secondary outcomes.

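### The trial is sized on the food-literacy score at T1 but tests change from baseline, so power is below plan if the T0–T1 correlation is under 0.5; adjusting for the T0 score is more precise

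*Protocol article*

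**What the plan says.** **Sizing (Protocol article, Sample Size Calculation).** The SD comes from reference values: "Sample size calculation is based on the known mean value and SD of the SPFLS (food literacy measure) for the Dutch general population". For the control arm the assumption reads "an anticipated mean of 3.83 (SD 0.41) in the control group is expected at T1"; for the intervention arm it reads "an anticipated mean of 4.20 SPFLS score in the intervention group". These give the standardised effect: "it seemed reasonable to expect an effect size of 0.9". The result is "With a standard power of 80% and a significance level of 5%, a total of 19 participants per group", raised to 28 per group for 30% dropout. No SD of change and no T0–T1 correlation is used.

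**Analysis (Protocol article, Statistical Analyses).** The tested contrast is described as follows: "The mixed models will test the difference compared with baseline in the scores and values (ie, dependent variables) between intervention and control", at T1 and T2. T0 is listed with T1 and T2 among each participant's repeated measures. The covariates named as examples are sex, age, education and BMI. The outcome's own T0 value is not among them. It could enter only through a further rule: "Variables that statistically significantly differed at baseline are also included in a model as covariates". The test level is also given: "Two-sided *P* values <.05 are regarded as statistically significant".

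**The concern.** The two sections describe different contrasts. A between-arm comparison of T1 scores has the cross-sectional SD. A between-arm comparison of change subtracts T0 with a fixed slope of 1, and its SD depends on ρ. The power in the article therefore belongs to a comparison that the analysis section does not make.

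The change contrast also uses the T0 score less efficiently than the data allow. When ρ is below 1, subtracting the whole of T0 over-corrects. An arm that starts low by chance tends to show a larger gain through regression to the mean. With 56 participants, chance differences at T0 are not negligible against a target of 0.37.

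The rule on baseline imbalance does not solve this. If T0 is one of the modelled outcomes, a participant-level main-effect covariate cancels out of a within-person change in complete data. T0 SPFLS would also stand on both sides of the model. These problems remain even when the arm-by-visit terms needed for a change contrast are correctly fitted.

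**Working it through.** **Inputs from the article.** Difference 4.20 − 3.83 = 0.37; SD 0.41; two-sided 5%; 19 completers per arm, 28 randomised per arm.

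**Assumptions.** Equal SDs of 0.41 at T0 and T1. ρ is not given, so it is shown from 0.2 to 0.7.

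**The plan's own figure.** 0.37/0.41 = 0.902. For 80% power the normal approximation gives 20 per arm and the noncentral t gives 21, so the stated 19 is reproduced within 2. At 19 per arm, power is 79.4% (normal) or 77.2% (noncentral t). Dropout: 19/0.70 = 27.1, rounded up to 28. Losses due to the contrast should therefore be read against 77%, not 80%.

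**The two contrasts.**
- Change: SD = 0.41·√(2(1−ρ))
- Adjusted for T0: SD = 0.41·√(1−ρ²)
- Variance ratio, adjusted to change: (1−ρ²)/(2(1−ρ)) = (1+ρ)/2

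Power by noncentral t at 19 per arm (36 df for change, 35 df for adjusted):

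| Assumed ρ | SD of change | Power, change | SD adjusted | Power, adjusted | (1+ρ)/2 |
|---|---|---|---|---|---|
| 0.2 | 0.519 | 57% | 0.402 | 79% | 0.60 |
| 0.3 | 0.485 | 63% | 0.391 | 81% | 0.65 |
| 0.4 | 0.449 | 70% | 0.376 | 84% | 0.70 |
| 0.5 | 0.410 | 77% | 0.355 | 88% | 0.75 |
| 0.6 | 0.367 | 86% | 0.328 | 92% | 0.80 |
| 0.7 | 0.318 | 94% | 0.293 | 97% | 0.85 |

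Estimating the slope on T0 multiplies the adjusted variance by about 1 + 1/34 at this size. Adjusted power then becomes 78%, 80%, 83%, 87%, 92% and 96%. The variance gain at ρ = 0.7 becomes 1 − 0.85 × 1.029 ≈ 12%, not 15%.

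**Does a mixed model recover the precision by itself?** No. Generalised least squares with T0, T1 and T2 as outcomes, compound symmetry and arm-by-visit terms gives, at ρ = 0.5, a standard error of 0.1330 for the T1-minus-T0 contrast. This equals the change-score formula, 0.410·√(2/19). Constraining both arms to one T0 mean gives 0.1152, which equals the adjusted formula.

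**Chance imbalance at T0.** With 28 per arm, the T0 difference has SD 0.41·√(2/28) = 0.11. For a given T0 difference D, the change contrast is displaced on average by (1−ρ)·D in the opposite direction. A one-SD difference therefore moves it by 0.077 at ρ = 0.3 (21% of 0.37) and by 0.033 at ρ = 0.7 (9%).

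If the T0 difference is statistically significant, its mean size is about 2.34 × 0.11 = 0.256 by the normal approximation. At ρ = 0.5 the expected change estimate is then 0.37 ± 0.5 × 0.256, that is 0.24 or 0.50.

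**The covariate rule.** In one simulated complete data set (28 per arm, random intercept, arm-by-visit terms), the T1 change contrast was 0.36129 (SE 0.1033) with no covariate, with age, with T0 SPFLS, and with both. Proper adjustment for T0 gave 0.336 (SE 0.088).

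**The case against.** - **The power loss is hypothetical.** Nothing in the article shows that ρ is below 0.5, and above 0.5 the change contrast exceeds the plan. This stands: the fault is a mismatch, not a proven lack of power.
- **The trial may keep more than 19 per arm.** If all 28 were retained, change-contrast power would be 80% at ρ = 0.3 and 86% at 0.4. This is the favourable bound, since the plan itself allows for 30% dropout. It is still below the 91% of a T1 comparison at 28 per arm and the 93% of the adjusted contrast at ρ = 0.3.
- **The change contrast is valid.** Under randomisation it has the same expectation as the T1 difference, and its standard error already covers chance imbalance. The 0.24 or 0.50 illustration conditions on an event of 5% probability, equally likely in either direction. This is correct. The point concerns precision and a misplaced power statement, not bias.
- **The model is not fully fixed.** The listed fixed effects name no treatment-by-time term, and the sentence can be read as making change itself the dependent variable. On that reading, adding T0 as a covariate would give the adjusted estimate exactly, so the remark that a covariate cannot repair the contrast would fail. The listing of T0 among the repeated measures favours the reading used here. On either reading, the T0 score is not a standing covariate.
- **A fuller analysis protocol is mentioned but not shown.** It may state ρ. The contrast, the place of T0, the covariate rule and the SD used for sizing are nevertheless stated in the article, and they do not fit together.

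**Conclusion.** The concern holds. The article's power belongs to a T1 comparison, while the analysis tests change from baseline. With SD 0.41 at both visits and 19 completers per arm, the change contrast has 57% to 70% power at ρ of 0.2 to 0.4, 77% at 0.5 (the same as the T1 comparison), and 86% to 94% at 0.6 to 0.7. Whether power is actually lost is unknown, because ρ is not given.

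The case for adjusting does not depend on ρ. The variance falls by 15% to 40% over this range in theory, or about 12% to 38% after paying for the estimated slope. The missing treatment-by-time term is a separate matter and does not affect this conclusion. The change should be made; it is an improvement in precision rather than a correction of bias.

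**What to change.** 1. For SPFLS and each secondary outcome, model T1 and T2 as the repeated outcomes. Include the outcome's own T0 value and its interaction with visit as fixed covariates in every model, including the crude one. Report the adjusted arm difference at T1 and at T2.
2. Equivalently, keep T0 among the outcomes but constrain both arms to one common T0 mean. This version retains participants who have only a T0 measurement; the covariate version loses them.
3. Restate the power for this contrast, using SD 0.41·√(1−ρ²) and naming the assumed ρ.

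The cost is one changed line in the analysis script and one sentence in the sample-size text, with no new data. The article reports that data acquisition ended on August 1, 2022, so the sample size can no longer change. The analysis is described as still to come, so the model should be fixed before the blinded primary analysis is run and the treatment codes are broken.
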